## Abstract

**Background:**

Low levels of physical activity are common in patients with chronic obstructive pulmonary disease (COPD), and a sedentary lifestyle is associated with poor outcomes including increased mortality, frequent hospitalizations, and poor health-related quality of life. Internet-mediated physical activity interventions may increase physical activity and improve health outcomes in persons with COPD.

**Methods/Design:**

This manuscript describes the design and rationale of a randomized controlled trial that tests the effectiveness of Taking Healthy Steps, an Internet-mediated walking program for Veterans with COPD. Taking Healthy Steps includes an uploading pedometer, a website, and an online community. Eligible and consented patients wear a pedometer to obtain one week of baseline data and then are randomized on a 2:1 ratio to Taking Healthy Steps or to a wait list control. The intervention arm receives iterative step-count feedback; individualized step-count goals, motivational and informational messages, and access to an online community. Wait list controls are notified that they are enrolled, but that their intervention will start in one year; however, they keep the pedometer and have access to a static webpage.

**Discussion:**

Participants include 239 Veterans (mean age 66.7 years, 93.7% male) with 155 randomized to Taking Healthy Steps and 84 to the wait list control arm; rural-living (45.2%); ever-smokers (93.3%); and current smokers (25.1%). Baseline mean St. George’s Respiratory Questionnaire Total Score was 46.0; 30.5% reported severe dyspnea; and the average number of comorbid conditions was 4.9. Mean baseline daily step counts was 3497 (+/- 2220).

Veterans with COPD can be recruited to participate in an online walking program. We successfully recruited a cohort of older Veterans with a significant level of disability including Veterans who live in rural areas using a remote national recruitment strategy.

**Trial registration:**

Clinical Trials.gov NCT01102777

## Background

### Burden and management of COPD

Chronic Obstructive Pulmonary Disease (COPD) is a significant problem worldwide, affecting 9-10% of the population 40 years of age or older [1,2]. In the U.S., COPD is currently the third cause of mortality [3] and affects 5.1% of the population. Among Veterans the prevalence is 8.2% [4] with those afflicted by the disease accumulating more emergency room and outpatient visits to physicians when compared to persons without COPD. COPD is characterized by acute exacerbations (AECOPD), which are responsible for 70% of the total cost generated by the disease. AECOPD accelerate the rate of decline of lung function [5] and negatively impact health-related quality of life (HRQL); nearly 50% of the patients will continue to need help with their activities of daily living six months after hospital discharge for an AECOPD [6]. AECOPD are part of a downward spiral in functionality and HRQL and are also the main risk factor for new or recurrent exacerbations [7].

The principles of COPD management include control of symptoms, prevention of AECOPD, and improving HRQL. Strategies include smoking cessation, pharmacological therapy with short- and long-acting bronchodilators and anti-inflammatory inhaled medications, oxygen supplementation, and early recognition of symptoms. Almost all available therapeutic options have been proven to reduce symptoms, decrease the frequency of exacerbations, and improve HRQL [8-11], but none of the available pharmacologic interventions modifies the progressive loss of pulmonary function [12]. The recognition of a high frequency of cardiovascular disease as cause of death in COPD patients [13] and the role of comorbid conditions as risk factors for recurrent exacerbations has strengthened the interest in the management of other coexistent conditions as an alternative to improve the prognosis of patients with COPD [14], or to develop COPD self-management programs [15]. Engagement in physical activity is a cornerstone of self-management programs to improve health status.

### Exercise and physical activity in COPD

Persons with COPD have significant reductions in physical activity compared to controls [16,17]. Comorbidities of cardiovascular disease, musculoskeletal disease, osteoporosis [18], loss of skeletal muscle mass [19], muscle weakness, and weight loss [20] contribute to loss of functional capacity. Epidemiological and cross-sectional data have shown that physical activity is related to outcomes in COPD. Those who have higher levels of physical activity have a lower risk of hospital readmissions, acute exacerbations, and COPD-related hospitalizations [21]. Physical activity levels are the strongest predictor of mortality, independent of lung function [22].

This association between physical activity and COPD outcomes may be mediated through improved cardiorespiratory fitness or through reduced systemic inflammation [23]. Despite the benefits of physical activity, few interventions exist to promote physical activity in persons with COPD. Pulmonary rehabilitation has been clearly shown to improve exercise capacity, reduce dyspnea, and improve HRQL in persons with COPD [24]. Pulmonary rehabilitation includes exercise training for deconditioning, disease management education, management of dyspnea, appropriate use of medication, and identification of depression and other barriers to exercise. Pulmonary rehabilitation is a potent intervention. The number-needed-to-treat (NNT) with pulmonary rehabilitation to prevent one hospital admission is 4 (95% CI 3–8) [25].

### Limitations to exercise among COPD patients

Unfortunately, pulmonary rehabilitation programs are typically hospital based and are not accessible to everyone who needs them. In addition, the benefits gained after a typical 12-week supervised program plateau and begin to diminish after 9–12 months [26]. In a national survey of COPD patients more than 25% were not aware of the existence of rehabilitation programs, and an additional 13% reported that pulmonary rehabilitation programs were not available [27]. Criteria for participation in rehabilitation programs are usually determined by third party payers, and insurance could be a factor in receiving the intervention. Individual barriers identified in some studies include the need to make changes in the daily routine, competing needs and duties, and transportation problems [28]. Social isolation and living in remote areas is common in COPD patients, with up to 28% of Veterans with COPD residing in rural and isolated areas [29]. Living in rural or isolated areas is associated with a lower probability of receiving home health services and less frequent visits to physicians [30]. Finally, a systematic review identified lack of support and program-specific barriers as factors limiting participation in rehabilitation, while belief in personal benefits and setting goals are enablers for participation [31]. As a result, less than 13% of the potential candidates who might benefit from rehabilitation are referred by their health care provider [32]. Development of individual, home-based physical activity programs may address some of the barriers and may expand the reach to those living far from facilities that offer formal pulmonary rehabilitation programs. The Internet and other new forms of information and communication technology could provide a way to reach this population. A few studies have demonstrated the feasibility, acceptability, and efficacy of Internet-mediated smoking cessation and dyspnea management interventions in COPD [33,34]. Additionally, we have demonstrated the accuracy of the Omron HJ-720-ITC in a pilot study of 24 patients with COPD. At walking speed the pedometer was able to capture more than 80% of manual step counts, and the patients were able to upload the information [35]. In another study with 90-day follow-up, 27 older Veterans (mean age 72, s.d. 8 years) demonstrated the ability to regularly upload pedometer step counts to their home computer, and to be part of a feedback Internet-mediated program. They were also satisfied with the intervention and would recommend a similar program to potential participants [36].

Based on the previously reviewed evidence of the benefits of exercise as part of rehabilitation programs and recognizing the multiple barriers to participation in exercise programs faced by older patients, we designed the current pedometer-based, Internet-mediated intervention to promote walking in this population. The long-term objectives are to develop, test, and disseminate effective, low-cost interventions that improve HRQL for Veterans, particularly rural-living Veterans managing complex chronic conditions, which could be extrapolated to other similar populations.

## Methods

### Study design

Taking Healthy Steps is a randomized controlled clinical trial for Veterans with COPD across the U.S. The coordinating center is located at the VA Center for Clinical Management Research in Ann Arbor, Michigan.

### Conceptual framework

The Taking Healthy Steps intervention is based primarily on self-regulation theory. The Theory of Self-Regulation emphasizes an iterative, rational process of behavior change in which an individual working towards a behavioral goal learns from successes and failures and uses this knowledge to develop effective behavioral strategies to achieve his or her goal [37,38] (Figure 1). Accurate self-monitoring, goal setting, and feedback are critical components of the cycle of self-regulation. The Taking Healthy Steps intervention targets the cycle of self-regulation with four components: 1) step-count feedback from a pedometer and personal website, 2) automated, gradually incrementing goals, 3) tailored motivational messages, and 4) an online community to enhance social support. Participants upload detailed time-stamped step-count data. Tailored algorithms based on the data provide dynamic individualized incremental walking goals and feedback about success at meeting these goals. Goal setting is based on Lock and Latham’s demonstration that high, hard goals improve performance as long as the goals are not too high [39]. Goal increment is based on a series of pilot studies in individuals with a variety of chronic illness [40]. Online communities allow users to interact with each other by posting messages for others to read and by reading messages posted by others. These communities are useful for individuals who report low baseline social support, which is a predictor of poor adherence to physical activity interventions.

**Figure 1 F1:**
[figure not shown]
Conceptual Model for Taking Healthy Steps.

### Study aims

The specific aims of the current clinical trial are:

1. To test the effectiveness of an automated, internet-mediated walking program on HRQL at four months and at one year

2. To estimate the effect of the Taking Healthy Steps program on all cause days of hospitalization over one year in Veterans with COPD

3. To compare intervention reach, participation, and satisfaction between rural and urban Veterans among those randomized to the intervention arm

### Identification of target population

The flow of patients through the study is described in Figure 2. Potential participants are identified from VA national databases of patients who received care within the year prior to enrollment from a primary care provider, cardiologist, or pulmonologist within the VA health care system. The diagnosis of COPD is based on data extracted from ICD9 codes of 491.x Chronic Bronchitis, 492.x Emphysema and 496.x Chronic Airway Obstruction NEC indicating the likely presence of COPD. The identification of COPD patients using a similar algorithm has been associated with appropriate diagnostic accuracy (area under the ROC curve 0.75) [41]. Veterans less than 40 years old (to minimize misclassification with asthma) and individuals with diagnosis codes for quadriplegia and paraplegia, wheelchair dependence, dementia, or pregnancy-related diagnoses or procedures within the previous year were not eligible. We also excluded Veterans from VISN 01 facilities, where another COPD study using the Taking Healthy Steps platform was actively recruiting participants. After identifying potential participants, their zip codes were matched to Rural Urban Commuting Codes (RUCA), a validated algorithm developed by the U.S. Department of Agriculture – Economic Research Service to classify U.S. census tracts using measures of population density, urbanization, and daily commuting [42], which identified potential participants as living in urban or rural areas.

**Figure 2 F2:**
[figure not shown]
CONSORT diagram of the enrollment and allocation in the Taking Healthy Steps clinical trial.

Based on reported response rates of 2-5% in similar surveys of COPD patients, a random subset of 30,000 Veterans (half urban and half rural) was selected from the pool to receive mailed invitations to participate in the program. The invitation letter includes a brief description of the study and key eligibility criteria, as well as a website address to visit for more information, a six-digit numeric ID code to enter into the online form that allows them to proceed with further eligibility screening, and a pamphlet about research within the VA system. This remote recruitment strategy was intentionally designed to expand the reach to rural Veterans. Letter recipients who visit the website read an expanded description of the study. If interested, they enter their email address into a web form and complete an online screening questionnaire that assesses their demographics, health status, physical activity level, and computer access.

### Eligibility

Eligibility requirements include: Veteran; age ≥ 40 years old; diagnosis of COPD, emphysema, or chronic bronchitis based on administrative ICD-9 codes or self-report; able to walk a minimum of one block; sedentary (defined by < 150 minutes of self-reported physical activity per week); have a doctor or primary care provider who can give medical clearance; competent to give informed consent, and not having a legal guardian; regular email user (checking weekly); have access to a computer with an Internet connection, a USB port, and Windows XP, Vista, 7, or 8; not involved in another pedometer-based walking program.

Upon submission of the eligibility survey responses, an algorithm determines eligibility in real time. The website then directs eligible individuals to an online consent form with a click-through agreement and the opportunity to have study staff contact them to answer questions. Eligible participants present a medical clearance form to their health care provider to receive confirmation that the walking program is safe for them, and the signed form is faxed back to the coordinating center. A similar procedure of medical clearance has been previously tested in other studies by our group [43].

### Baseline measures and randomization

After completing the online screening and informed consent, participants complete online surveys about the primary outcome of HRQL using the St. George’s Respiratory Questionnaire and the general health status question from the SF-36. The surveys also assess demographics; health history including comorbidities and COPD hospitalizations; motivations and barriers for walking; knowledge and attitudes about COPD, current cigarette smoking, current supplemental oxygen use, the Modified Medical Research Council (MMRC) dyspnea score, depression, social support; and comfort with computers. Once the baseline survey is complete, study staff mail participants an Omron pedometer (HJ-720 ITC) with a USB upload cable and instructions about uploading pedometer data and pedometer care and use. This pedometer has been previously validated in a similar population [44]. Participants are asked to wear their pedometers throughout the day for seven days to assess their baseline step counts. Pedometers have a sticker over the display during the baseline assessment period, and no step-count goals or feedback are provided during this stage. At the end of the seven days the participant uploads their pedometer data using the USB cable and their computer. Immediately after completion of baseline pedometer data collection and receipt of the medical clearance, the participants are automatically randomized to one of two arms: 1) Internet-mediated, pedometer-enhanced program (Taking Healthy Steps) or 2) Wait list control. Randomization is stratified by breathlessness (defined by MMRC) and urban vs. rural residence.

### Pedometer-based, internet-mediated intervention (Taking Healthy Steps)

After being randomized to Taking Healthy Steps, participants receive an automated email message informing them of their first step-count goal and instructing them to remove the sticker from their pedometer. They also gain full access to their personal home page with individualized step-count goals, step-count feedback, graphs, and motivational messages. Participants receive two kinds of *tailored messages* on the website: a weekly motivational and an every-other-day informational message. The weekly *motivational* messages are based on individual responses to the baseline survey and address specific characteristics such as oxygen use and cigarette smoking, motivations, and barriers reported by the individual participant, highlighting benefits of exercise while addressing perceived personal barriers and strategies to overcome those barriers. A new *informational* message appears on the study home page every other day; some of these messages contain disease-specific content related to COPD while others are generic information about walking and health. Disease-specific content includes education about the potential benefits of walking for persons with COPD and overcoming COPD-specific barriers to walking (fear of becoming short of breath, fear of running out of oxygen in a public place, embarrassment with use of oxygen tank in public places). In addition, information is provided on specific problems (use inhaler before starting out on a walk), anticipated problems (walk an unknown course with a spouse first, walking on different surfaces and during different seasons), and building confidence in participating in a regular walking program (walk a specific route that you know you can complete without becoming short of breath). Where possible, content is evidence-based and modeled on content used in previously published COPD self-management and pulmonary rehabilitation studies. An example of the messages is displayed in Figure 3. Both the motivational and informational messages address barriers to walking that we have identified as being significant to COPD patients in a similar trial [45].

**Figure 3 F3:**
[figure not shown]
Example of the informational messages provided for participants in Taking Healthy Steps.

Participants are asked to wear the pedometer every day, from waking to sleeping, during the initial 16-week period of intervention, and are encouraged to continue wearing and uploading the data throughout the eight-month maintenance phase.

*Feedback* is provided in three ways: 1) participants can read their step-count data from the pedometer display throughout the day; after uploading step-count data to the website, they can select from a variety of detailed graphs displaying different views of their step counts, including weekly and daily views with daily or hourly step-count totals; 2) participants can look back at their graphs and goals from previous weeks; and 3) the website displays a textual message about their step-count average for the week.

*Goal-setting* is provided each week for the entire one-year intervention period, with participants receiving a new individually tailored and automatically calculated daily step-count goal. The algorithm for calculating step-count goals was developed based on a series of usability studies, pilot studies, and RCTs in participants with type 2 diabetes, coronary artery disease, and obesity [40,46]. This algorithm has been validated for use in similar populations [43]. The algorithm involves adding a fixed increment to the average step counts of uploaded pedometer data for the participant over the previous seven days. Because COPD patients tend to be less physically active and may find it more challenging to increase their step counts, the goal is never higher than a 600-step increment, rather than the 800- or 1200-step increments reported for other populations. Goals are rounded off to the nearest 100 steps, and the maximum possible goal is 10,000 steps per day. Each Sunday, the goal calculation algorithm is run and sends participants automated emails with their personalized daily step-count goal for the week, which appears in the step-count feedback section on the website, both in text form and graphs. Goals are not necessarily monotonically increasing. For example, if a participant is sick, and thus records low step counts for one week, the subsequent week’s goal might be lower than the goal for the week the participant was sick. A snapshot of the individual step-count webpage can be seen in Figure 4.

**Figure 4 F4:**
[figure not shown]
Example of the step-counts screen for participants in Taking Healthy Steps.

Additionally, all participants randomized to the intervention arm have access to *online community features*. They are able to read and post messages on the community message board under three different sections: Help Desk, Meet and Greet, and Sidewalk Talk. Study staff moderate and seed the message board. They also respond to some posts directly and stage competitions to encourage posting. The use of online communities has previously increased program retention in similar studies [47]. Finally, all participants who are randomized to the intervention arm have access to the study staff for questions, which could be initiated by sending an email or directly on the website through a form. Participants can also call the staff on a toll-free number. A screenshot of the online communities is presented in Figure 5.

**Figure 5 F5:**
[figure not shown]
Example of the online communities and forums for participants in Taking Healthy Steps.

### Wait list (control arm)

Wait list controls are notified that they are enrolled in the study, but that they will not be able to start the active intervention for one year. They are neither assigned step-count goals nor do they have access to the personalized dynamic website during the year long waiting period. However, they have access to a brief static webpage that provides a checklist of completed surveys and their week number in the study. Participants keep the study pedometer and are asked to log in monthly to report adverse events and to upload their pedometer data, with no other incentive to log into the website and no feedback of pedometer data or goal setting. They are given no specific instructions on exercise.

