### Outcomes and data collection procedures

The *primary outcome* is change in Saint George’s Respiratory Questionnaire (SGRQ) Total Score at 4 and 12 months compared to baseline. The SGRQ is a well validated disease-specific HRQL measure [48] widely used in clinical trials of pulmonary rehabilitation, disease management interventions, and exercise [49] in patients with COPD. SGRQ will be measured at baseline, four months, and one year after randomization.

Hospitalizations for AECOPD, self-reported dyspnea, and change in average daily step counts will be *secondary outcomes*. To ascertain hospital admissions, a two-way process will be performed, using both self-reported hospitalizations (which capture non-VA admissions) and identifying hospital admissions through the VA administrative databases. ICD-9 codes will be used to identify cause of admission. AECOPD will be defined by a previously validated combination of inpatient and outpatient ICD-9 codes [50], and validated algorithms will also be used to identify pneumonias and episodes of respiratory failure [51,52]. Dyspnea is measured with the MMRC Dyspnea Score [53,54]. Change in average daily step counts will be calculated using 7 days where at least 5 of the 7 days have at least 100 steps and 8 hours of activity. Goal commitment (percentage of intervention days during which step-count goals are achieved, as well as self-reported goal commitment and perceived difficulty of goal level evaluated by the Likert scale and open-ended questions) and participant retention are also secondary outcomes. Endpoints are evaluated at baseline, four months, and one year after randomization.

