### Monitoring and reporting of adverse events

Participants can report an adverse event (AE) by phone, website, or email, and are invited to do so every 30 days. The AEs are tracked electronically in a participant management system and classified as serious if they require hospitalization or result in significant disability or classified as minor if they result in minimal or no disability and do not require hospitalization.

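### Adverse-event counts by arm, and admissions known only from self-report, are open to differential ascertainment because site and staff contact differs by design

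*Protocol article*

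**What the plan says.** All references are to the Protocol article.

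**Reporting route.** Monitoring and reporting of adverse events makes no distinction by arm: "Participants can report an adverse event (AE) by phone, website, or email, and are invited to do so every 30 days". Reports enter an electronic tracking system and are classed as serious or minor, with hospitalization one of the criteria for serious. No other source of adverse events is described.

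**Intervention contact.** The section on the pedometer-based, internet-mediated intervention describes several layers:
- The goal algorithm runs every Sunday for the whole year and "sends participants automated emails with their personalized daily step-count goal for the week".
- A new informational "message appears on the study home page every other day".
- There is a message board, with a help section, that staff moderate and seed.
- In addition, "all participants who are randomized to the intervention arm have access to the study staff for questions", by email, web form or toll-free line.

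**Wait-list contact.** Under Wait list (control arm), "they have access to a brief static webpage that provides a checklist of completed surveys and their week number in the study". A log-in is requested once a month, for adverse-event reports and step uploads. The section adds that this request comes "with no other incentive to log into the website and no feedback of pedometer data or goal setting".

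**Admissions.** Outcomes and data collection procedures specifies two sources: "self-reported hospitalizations (which capture non-VA admissions") and the VA administrative databases. How and when the self-reports are collected is not stated. Endpoints are assessed at baseline, four months and one year. The Analysis plan compares hospital days between arms by Poisson or negative binomial regression, with follow-up days as the offset.

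**The concern.** When events are counted from what participants tell the study, an arm with more reasons to visit the site and more contact with staff has more occasions to mention an event. At the same true event rate, that can yield more recorded events.

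Two results are exposed:

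- **Safety summary by arm.** An excess of reports on the intervention could be read as harm from walking when it reflects contact.
- **Aim 2, all-cause hospital days.** Admissions in the VA databases do not depend on log-in, but a non-VA stay enters only if the participant reports it. Because the offset is follow-up time, an unreported non-VA stay counts as zero days with full person-time. If controls under-report more, a true reduction in hospital days on the intervention would look smaller than it is.

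Adjusting for baseline covariates would not repair this, because the difference arises after randomization and lies in the measurement.

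**Working it through.** The plan gives no figure on this point to reproduce. The check compares contact by arm, then asks how far unequal capture could move each count.

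**Contact by arm**

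| Feature | Intervention | Wait list |
|---|---|---|
| Channels for adverse events | phone, website, email | phone, website, email |
| Invitation to report | every 30 days, 365/30 ≈ 12 a year | every 30 days, ≈ 12 a year |
| Goal emails | weekly, 365/7 ≈ 52 a year | none |
| Web content | goals, graphs, renewed messages, board | static page |
| Staff access for questions | email, form, toll-free line | none described |

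Solicitation is equal and other contact is not. This shows unequal opportunity to report. It does not show unequal reporting, since no log-in or response rates by arm are given.

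**Illustration with assumed inputs**

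Assume no true difference between arms. Let c_int and c_ctl be the completeness of self-report in each arm, and v the share of hospital days found in the VA databases, taken as fully captured there. None of these values is in the article.

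- Apparent adverse-event ratio = c_int / c_ctl
- Apparent hospital-days ratio = [v + (1 − v) × c_int] / [v + (1 − v) × c_ctl]

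| c_int vs c_ctl | Adverse events | Days, v = 0.25 | v = 0.50 | v = 0.75 | v = 0.90 | v = 1 |
|---|---|---|---|---|---|---|
| 0.90 vs 0.90 | 1.00 | 1.00 | 1.00 | 1.00 | 1.00 | 1.00 |
| 0.90 vs 0.80 | 1.13 | 1.09 | 1.06 | 1.03 | 1.01 | 1.00 |
| 0.90 vs 0.70 | 1.29 | 1.19 | 1.12 | 1.05 | 1.02 | 1.00 |
| 0.90 vs 0.50 | 1.80 | 1.48 | 1.27 | 1.11 | 1.04 | 1.00 |

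Worked cases:
- Adverse events: 0.90/0.80 = 1.13 and 0.90/0.70 = 1.29.
- Days, 30% outside VA records, 0.90 vs 0.80: (0.70 + 0.27)/(0.70 + 0.24) = 0.97/0.94 = 1.03.
- Days, 50% outside, 0.90 vs 0.70: (0.50 + 0.45)/(0.50 + 0.35) = 0.95/0.85 = 1.12.
- A true days ratio of 0.80 with 0.90 vs 0.70: with half in VA records it appears as 0.80 × 0.95/0.85 = 0.89; with 90% in VA records, as 0.80 × 0.99/0.97 = 0.82.
- Direction reversed, 0.80 vs 0.90: adverse-event ratio 0.80/0.90 = 0.89.

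The adverse-event count takes the full effect of any gap. The hospital-days ratio takes less as VA coverage rises, and none when coverage is complete. The hospital-days columns apply only if the reporting gap also affects how self-reported admissions are collected.

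**The case against.** A reader might infer more than this: that the intervention arm uses the reporting channels far more, that the plan pools all reports, and that the counts are therefore biased. The documents do not support that reading.

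- Both arms have the same three channels and the same 30-day invitation. Equal solicitation is the usual safeguard and it is already in place. The toll-free line is listed for the intervention arm, but every participant may report adverse events by phone.
- Controls are asked to log in each month specifically to report events, whereas intervention visits serve goals, graphs and messages. Intervention participants who disengage may also under-report. The direction is therefore likely but not certain.
- No pooling rule is stated, and no between-arm test of adverse events appears in the aims, outcomes or analysis plan. The point concerns any summary by arm, not a planned test.
- Self-reported admissions may come from the four-month and one-year assessments common to both arms, which is at least as plausible as the adverse-event route. The baseline survey already asks about COPD hospitalizations. In that case the Aim 2 part of the concern shrinks.
- The VA database search already protects part of the hospital-days outcome.

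All of this stands, and it limits the claim to a risk of unknown size. It does not remove the risk: adverse events have no second source described, and the difference in contact is a stated design feature rather than an omitted detail.

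**Conclusion.** The point holds as a risk of differential ascertainment, with medium confidence. It applies to adverse-event counts by arm and, depending on how they are collected, to admissions known only from self-report (chiefly non-VA stays). More recorded events on the intervention is the likely direction.

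The document does not allow the size to be computed. The ratios of 1.13 to 1.29 for adverse events and 1.03 to 1.12 for hospital days rest wholly on assumed capture of 90% against 70–80% and an assumed 30–50% of hospital days outside VA records. With equal capture both ratios are 1.00. If most admissions are in VA records, the effect on Aim 2 is small.

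The primary SGRQ outcome is not affected by this point. The change is still worth making, because it is cheap and protects a safety summary and a named aim.

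**What to change.** 1. Keep every event in the safety record and in the overall count.
2. Flag each adverse event and each self-reported admission as solicited (30-day prompt or scheduled survey) or spontaneous.
3. Present the by-arm summary for solicited reports alongside the one for all reports, and give prompt response rates by arm. Response to the prompt may itself differ by arm, so the solicited count reduces the problem without removing it.
4. Pre-specify, as a sensitivity analysis, the hospital-days regression of the Analysis plan on VA-recorded admissions alone. That result does not depend on contact with the study.
5. Keep follow-up days as the offset. Limiting person-time to answered prompts may look attractive, but it conditions on a post-randomization response. Participants who are in hospital or very ill may be the least likely to answer, so intervals rich in events could drop out.

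The cost is one source flag in the existing tracking system and one extra analysis. The VA-only analysis omits non-VA stays, so it is less complete and should stand beside the combined analysis rather than replace it.
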